# Comparison between the standard and a new alternative format of the Summary-of-Findings tables in Cochrane review users: study protocol for a randomized controlled trial

**DOI:** 10.1186/s13063-015-0649-6

**Published:** 2015-04-16

**Keywords:** Summary-of-Findings table, Systematic review, Knowledge translation, Evidence summary, GRADE approach

## Abstract

**Background:**

Systematic reviews represent one of the most important tools for knowledge translation but users often struggle with understanding and interpreting their results. GRADE Summary-of-Findings tables have been developed to display results of systematic reviews in a concise and transparent manner. The current format of the Summary-of-Findings tables for presenting risks and quality of evidence improves understanding and assists users with finding key information from the systematic review. However, it has been suggested that additional methods to present risks and display results in the Summary-of-Findings tables are needed.

**Methods/Design:**

We will conduct a non-inferiority parallel-armed randomized controlled trial to determine whether an alternative format to present risks and display Summary-of-Findings tables is not inferior compared to the current standard format. We will measure participant understanding, accessibility of the information, satisfaction, and preference for both formats. We will invite systematic review users to participate (that is clinicians, guideline developers, and researchers). The data collection process will be undertaken using the online 'Survey Monkey' system. For the primary outcome understanding, non-inferiority of the alternative format (Table A) to the current standard format (Table C) of Summary-of-Findings tables will be claimed if the upper limit of a 1-sided 95% confidence interval (for the difference of proportion of participants answering correctly a given question) excluded a difference in favor of the current format of more than 10%.

**Discussion:**

This study represents an effort to provide systematic reviewers with additional options to display review results using Summary-of-Findings tables. In this way, review authors will have a variety of methods to present risks and more flexibility to choose the most appropriate table features to display (that is optional columns, risks expressions, complementary methods to display continuous outcomes, and so on).

**Trials registration:**

NCT02022631 (21 December 2013)

## Background

Systematic reviews play a major role in informing decision-making for clinicians, policy-makers, guideline developers, and other stakeholders [1,2]; however, their results are not always easy to understand and interpret. Studies regarding the use and interpretation of evidence to inform health care decisions have shown that text-reported information about a treatment effect is inconsistently interpreted [3,4], and numerical results of risks may be difficult to understand, even for educated users [5]. We previously [6] conducted a systematic review to study the effects of using alternative statistical presentations for reporting risk and risk reduction on understanding, perception, persuasiveness and behavior of health professionals, policy-makers, and consumers. Participants better understood risks expressed as natural frequencies (that is 15 out of 100) compared to risks expressed as probabilities (that is 15%). Relative risk reductions (RRR) were equally understood compared to absolute risk reductions (ARR), but better understood than number needed to treat (NNT), in particular when baseline risks were not shown. However, RRR were perceived as (misleadingly) larger and more persuasive than both ARR and NNT. These findings highlight the importance of appropriate presentation of systematic review results on users’ understanding, and perception.

The 'Grading of Recommendations Assessment, Development and Evaluation' (GRADE) system [7-12] is a widely accepted approach for developing and presenting summaries of evidence for both systematic reviews and clinical guidelines in a standardized and transparent manner [13]. The aim of this approach is to summarize the most important results from a systematic review in absolute and relative terms, be explicit about patient-important benefits and harms, and report the quality of the evidence (also called 'confidence in the effect estimates') for each outcome and across outcomes, in such a way that clinicians, policy- makers, and consumers can use reviews’ results efficiently and reliably. To accomplish this goal, the GRADE approach proposes the use of 'Summary-of-Findings' (SoF) tables and evidence profiles [14].

SoF tables have undergone deliberate development. The current format and content of SoF tables are based on user-testing studies, stakeholder feedback, and two randomized controlled trials [15-17]. These studies showed that SoF tables (incorporated in systematic reviews) significantly improved understanding (93% versus 44% (*P* = 0.003)) and the ability to find critical information (68% versus 40% (*P* = 0.021)) compared to those without SoF tables that report results only in a narrative way [17]. In another randomized trial, it was found that formatting modification of GRADE evidence profiles can increase the comprehension of key findings ranging between 5 to 47% [18].

Since 2004, The Cochrane Collaboration has been intensively working on the implementation of SoF tables in their reviews. By 2014, more than 600 SoF tables had been published across review groups (Langendam et al: Improving GRADE evidence tables: A systematic survey of explanatory footnotes and judgments in Summary of Findings Tables and Evidence Profiles shows more guidance is needed, manuscript in preparation). However, it has been noticed that the current standard format may need to be adapted depending on specific review characteristics. For example, the current SoF table format does not provide specific guidance for scenarios such as the narrative reporting of results when a meta-analysis was not undertaken nor alternative formats of presenting continuous and dichotomous outcomes. The inclusion of alternative presentations of risks in SoF tables included in systematic reviews would allow authors to choose from a variety of scientifically tested items that can be used to fit into the users’ needs.

Considering the above, the aim of this trial will be to determine whether new alternative SoF table format is not inferior compared to current standard format. Inferiority will be assessed by: understanding; perceived accessibility; satisfaction; and preference by health care professionals, guideline developers, and researchers that use and/or develop systematic reviews.

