### Participants

#### Selection criteria

Participants will be eligible if they consider themselves as systematic review users. For the purpose of this trial, a user is defined as someone who has used Cochrane and/or non-Cochrane systematic reviews at least twice a year to answer clinical questions on a patient-health professional basis, inform the process of making recommendations for clinical practice guidelines, inform other types of evidence-based decision-making, or to use them for research purposes. We will include three target populations: (1) health professionals working in primary, secondary, or tertiary care, (2) clinical practice guidelines developers, and (3) researchers. We will classify as clinicians those who report at least 50% of total time dedicated to clinical practice. To be considered a guideline developer, participants should declare having participated in at least 1 clinical practice guideline during the last 2 years. Finally, participants who declare dedicating more than 70% of their time to conduct research (for example, methodologists, epidemiologists, statisticians, and so on) will be classified as researchers. Compared to previous trials testing SoF tables, this study includes similar populations [17,18].

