The proportion of participants correctly answering questions about understanding in similar randomized controlled trials that tested the current SoF table format was between 80 to 87% [17,18], and we expect, at least, the same percentage in the group of participants randomized to the alternative format of SoF table. A non-inferiority margin of 10% was set, and an allocation of 1:1 participants will be used. If there is truly no difference between the current and the alternative table format, then 280 participants are required to be 80% sure that the upper limit of a 1-sided 95% confidence interval (CI) will exclude a difference in favor of the current SoF table format of more than 10%. Assuming that 10% of participants would not complete the questionnaire, we aim to recruit a total of 308 participants. Linear and logistic regressions will be used as a method of analysis. According to Hsieh *et al*. [22], when more than one covariate is included in the model, a variance inflation factor should be added to the typical univariate analysis to obtain the required sample size. Equation 3 represents the variance inflation factor cited, where *b*_1_ represents the maximum likelihood estimate of *β*_1,_ var_p_(*b*_1_) corresponds to the variance of *b*_1_ that it is approximated from a one parameter model to a multivariate case when multiplied by 1/(1 - ρ^2^_1.23….p_), where ρ_1.23….p_ is the multiple correlation coefficient associating *X*_1_ with *X*_2_,…*X*_p_.

From unvariate to multivariate regression model sample size estimation:3$$ \mathrm{v}\mathrm{a}{\mathrm{r}}_{\mathrm{p}}\left({b}_1\right) = \mathrm{v}\mathrm{a}{\mathrm{r}}_1\left({\mathrm{b}}_1\right)/\left(1\hbox{-} {\uprho^2}_{1.23\dots .\mathrm{p}}\right) $$

Since this is a clinical trial in which participants will be allocated to the study arms randomly, it can be assumed that no correlation exists between being assigned to a particular arm and any of the predictors considered for analysis. Then, the value of ρ in the current study is zero, and the estimated sample size is the one described above.

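### The 280 participants give 80% power only at 87% correct, the top of the plan's own 80 to 87% range; at 80% correct, or at the Bonferroni level planned for each question, power is well below that.

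*Protocol article*

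**What the plan says.** All references are to the protocol article.

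- **Planning rate (Sample size calculation).** The proportion answering understanding questions correctly is taken from what was seen "in similar randomized controlled trials that tested the current SoF table format was between 80 to 87% [17,18" (references 17 and 18). For the other arm, "we expect, at least, the same percentage in the group of participants randomized to the alternative format of SoF table".
- **Margin and true difference (same section).** "A non-inferiority margin of 10% was set", and the calculation is made under the condition "If there is truly no difference between the current and the alternative table format". With 1:1 allocation, 280 participants are said to give 80% power at a one-sided 95% confidence limit. Recruitment is set at 308 to allow for non-completion. The article does not say which rate within 80 to 87% produced 280.
- **Level used in the analysis (Inferential analysis).** Each of the seven understanding questions has its own logistic regression. The threshold is Bonferroni-corrected to below 0.0035, with confidence limits built on a one-sided z of 2.7.
- **Source trials (Background).** Reference 17 is reported as showing that SoF tables "significantly improved understanding (93% versus 44" per cent. Reference 18 is described as showing that "formatting modification of GRADE evidence profiles can increase the comprehension of key findings ranging between 5 to 47" per cent. The Selection criteria section puts both among SoF-table trials: "Compared to previous trials testing SoF tables, this study includes similar populations [17,18".

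**The concern.** The variance of a difference in proportions depends on the rate, and between 80% and 87% it changes by a large factor: p(1 − p) is 0.1600 at 80% and 0.1131 at 87%, a ratio of 1.41. One sample size cannot therefore give the same power across the whole range. If 280 belongs to the favourable end, the stated 80% is a best case presented as the general one.

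The level matters as well. A calculation at one-sided 0.05 does not describe a test carried out at 0.0035. What is at stake is interpretation. A reader who trusts the stated 80% would take a question that misses non-inferiority as some evidence against the new format, when that outcome may be more likely than not even if the two formats are equally good.

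The mismatch over references 17 and 18 adds a smaller difficulty: the reader cannot trace where the range comes from.

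**Working it through.** **Inputs.** Common rate p in both arms, 80 to 87% (Sample size calculation); true difference 0; margin 0.10; one-sided 0.05, z = 1.645; power 80%, z = 0.842; 140 per arm. The analysis level is one-sided 0.0035, z = 2.697, which the article rounds to 2.7 (Inferential analysis). The 93% comes from the Background.

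**Step 1: reproduce the plan's figure.** With unpooled variance,

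n per arm = 2p(1 − p)(1.645 + 0.842)² / 0.10².

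At p = 0.87: 2 × 0.1131 × 6.183 / 0.01 = 139.9, so 140 per arm and 280 in total. This matches exactly.

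**Step 2: find the rate that 280 requires.** Setting n = 140 gives p(1 − p) = 140 × 0.01 / (2 × 6.183) = 0.1132, so p = 0.870. Any lower rate in the range needs more than 280.

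**Step 3: the lower end.** At p = 0.80: 2 × 0.16 × 6.183 / 0.01 = 197.8, so 198 per arm and 396 in total.

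**Step 4: power of 280 at each level.** Power = Φ(0.10 / SE − z), with SE = √(2p(1 − p)/140).

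- p = 0.80: SE = 0.0478 and 0.10/SE = 2.092. At 0.05, Φ(0.447) = 0.67. At 0.0035, Φ(−0.605) = 0.27.
- p = 0.87: SE = 0.0402 and 0.10/SE = 2.488. At 0.05, Φ(0.843) = 0.80. At 0.0035, Φ(−0.209) = 0.42.

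| Rate correct, both arms | Total needed, one-sided 0.05 | Power of 280, 0.05 | Total needed, one-sided 0.0035 | Power of 280, 0.0035 |
|---|---|---|---|---|
| 80% | 396 | 67% | 802 | 27% |
| 83.5% (midpoint) | 342 | 73% | 692 | 33% |
| 87% | 280 | 80% | 568 | 42% |
| 93% (Background) | 162 | 95% | 328 | 72% |

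**Step 5: sensitivity to how the Bonferroni level is read.** The printed 0.0035 is close to 0.025/7 = 0.0036. If the one-sided 0.05 of the sample size section were divided by seven (0.0071, z = 2.45), the power of 280 would be 36% at 80% correct and 52% at 87%. The conclusion is the same.

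**Step 6: the sources, side by side.** The Background gives 93% for understanding, citing reference 17; the Sample size calculation cites the same reference, with 18, for 80 to 87%. The Background describes reference 18 as a trial of evidence profiles and gives only gains, with no absolute rate. The Sample size calculation says it tested the current SoF format, and the Selection criteria and Preference sections also class it with SoF-table studies.

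**The case against.** Four points can be made for the plan.

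First, 280 is not a miscalculation: at 87% it is exactly right under the stated inputs. That stands, and it is why the remedy concerns the statement about power rather than the number.

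Second, the plan expects the new format to do at least as well. If it is truly better, power is higher than shown. That also stands, but the stated 80% is expressly for no true difference, so it must be judged there.

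Third, the Abstract gives the non-inferiority rule with a one-sided 95% limit, and the Discussion concedes that multiplicity adjustment may leave results inconclusive. Both are fair. But the Inferential analysis section fixes z at 2.7 for the intervals, and the Discussion does not say how much power is lost. Showing both levels answers this.

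Fourth, the source mismatch may be only apparent. A reader might infer from the 93% that the planning range is wrong, that neither cited trial supports it, or that 280 is too small for that reason. The article supports none of these. The 93% may belong to one question or measure and the range to others or to an average. The Background gives no absolute rate for reference 18 that could compete with 80 to 87%. A rate of 93% would lower the required total to 162 and raise the power of 280 to 95% at one-sided 0.05. Only the cited trials could settle the matter, and they are not at hand.

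**Conclusion.** The statement that 280 participants give 80% power is true at 87% correct and at no lower rate in the plan's range. At one-sided 0.05, power runs from 67% at the bottom of the range to 80% at the top. At the level planned for each question it runs from about 27% to 42%, so under no true difference a question is more likely than not to miss non-inferiority anywhere in that range.

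These figures assume equal rates in both arms, 280 evaluable participants, an unadjusted difference in proportions with a normal approximation, and one question at a time. The rate will vary across the seven questions, so power will too.

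The disagreement between the Background and the Sample size calculation over references 17 and 18 is real but minor. It is a matter of sourcing, and it does not show which figure is right or that the sample size is wrong.

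**What to change.** Keep 280. In the Sample size calculation section:

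1. State the rate used for 280 (the figure corresponds to 87%).
2. Replace the single 80% statement with a short table of the power of 280 at 80%, 83.5% and 87%, at one-sided 0.05 (67%, 73%, 80%) and at 0.0035 (27%, 33%, 42%). If 93% is kept as a relevant rate, add it (95% and 72%).
3. Say which level governs the non-inferiority claim for each question, so that the Abstract, Sample size calculation and Inferential analysis sections agree.
4. Add one or two sentences saying what references 17 and 18 tested and how the 93% in the Background relates to 80 to 87%.

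The cost is one reworded paragraph and a small table. No extra participants are needed. The trial is still recruiting, so the text can be corrected before the data are analysed.

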## Methods

The following description of methods and analysis of this trial follows the latest guidance by the Consolidated Standards of Reporting Trials (CONSORT) group in its extension for reporting of non-inferiority and equivalence randomized trials [19] and the SPIRIT (Standard Protocol Items: Recommendations for Interventional Trials) statement [20]. The protocol of this study was registered in the clinicaltrials.gov database (NCT02022631).

### Overview of the design

We will conduct a parallel-armed, non-inferiority randomized trial comparing a new alternative format of SoF tables with current format. We will contact systematic review users by Email and ask them to fill a questionnaire developed using the 'Survey Monkey' online system. The data collection form will include questions about baseline information (demographic characteristics, background, familiarity with systematic reviews and the GRADE system, and so on). Then, participants will be randomly assigned to one of two SoF tables, either the one in the alternative format or the one with the current format (See Figure 1). Randomization will be stratified according to participants’ background (health professional, guideline developer, researcher). They will be asked to answer questions to determine understanding, accessibility of information, and satisfaction with the table format to which they were allocated. Finally, we will show them the other table format to which they were not initially allocated in order to test their preference for either one.

**Figure 1 Fig1:**
[figure not shown]
Study design and flow-chart.

### Participants

#### Selection criteria

Participants will be eligible if they consider themselves as systematic review users. For the purpose of this trial, a user is defined as someone who has used Cochrane and/or non-Cochrane systematic reviews at least twice a year to answer clinical questions on a patient-health professional basis, inform the process of making recommendations for clinical practice guidelines, inform other types of evidence-based decision-making, or to use them for research purposes. We will include three target populations: (1) health professionals working in primary, secondary, or tertiary care, (2) clinical practice guidelines developers, and (3) researchers. We will classify as clinicians those who report at least 50% of total time dedicated to clinical practice. To be considered a guideline developer, participants should declare having participated in at least 1 clinical practice guideline during the last 2 years. Finally, participants who declare dedicating more than 70% of their time to conduct research (for example, methodologists, epidemiologists, statisticians, and so on) will be classified as researchers. Compared to previous trials testing SoF tables, this study includes similar populations [17,18].

#### Setting and recruitment

We will recruit participants from Europe, North America, South America, Africa and Australasia. We will contact people through various networks: Cochrane review groups and the networks of the co-authors who interact with guideline developers, researchers and systematic reviewers. Potentially eligible participants will receive a structured and standardized invitation with a link to access the 'Survey Monkey' questionnaire. Using this online system, we will determine whether the participants are eligible based on the selection criteria. All eligible participants will be provided with a brief explanation of the study and an online informed consent. We will also recruit participants at workshops, conferences and other research events. The Hamilton Health Sciences/Faculty of Health Sciences Research Ethics Board at McMaster University reviewed the protocol and approved it to be conducted without need of official approval, arguing that this trial is a quality improvement study with almost no risk to participants. Based on this assessment, participant consent was also waived by the Ethics Board.

### Intervention and comparison

In this trial, one table displaying an alternative format of SoF will be tested against the current table format. In both SoF tables, the clinical question of the review in terms of patients, setting, intervention, comparator, outcomes, and the complementary information included as footnotes, will be the same. The only differences between the current and alternative SoF table formats will be the methods to either display the same data in a different way or to provide complementary data to the one shown in the current format (for example, risk difference). The SoF table in the current format that will be used in the control group is similar to the tables tested in previous trials on the same topic. With slight modifications, the SoF tables that will be used in this study are based on a real Cochrane systematic review conducted by Johnston *et al*. [21], titled *Probiotics for the prevention of pediatric antibiotic-associated diarrhea*. A comparison between the items included in the alternative and current SoF table formats is listed in Table 1. Figures 2 and 3 correspond to the alternative (Table A) and current formats (Table C) of SoF table formats respectively.

**Table 1 Tab1:** **Comparison between items included in the current and alternative Summary-of-Findings (SoF) table formats**

	**Current formats (Table C)**	**Alternative formats (Table A)**
1	Inclusion of the number of participants and studies column	Exclusion of the number of participants and studies column. Information presented in the outcomes column
2	Quality of evidence presented with symbols and labeled as High, Moderate, Low, or Very low. Reasons for downgrading presented in the footnotes	Quality of evidence presented along with main reasons for downgrading in the same column (for example, Moderate due to imprecision)
3	'Footnotes' label	'Explanations' label
4	Baseline risk and corresponding risk expressed as natural frequencies	Baseline risk and corresponding risk expressed as percentages
5	No column presenting absolute risk reduction (risk difference) or mean difference	Inclusion of a column presenting absolute risk reduction (risk difference) or mean difference
6	Comments column included	Comments column deleted
7	No 'What happens' column^a^	'What happens' column included^a^
8	Description of the GRADE Working Group grades of evidence definitions below the table	No description of the GRADE Working Group grades of evidence definitions

^a^The 'What happens' column aims to summarize both the treatment effect and the quality of the evidence in one short narrative statement.

